### Data collection and assessments

#### Biological samples.

Blood samples are collected via venipuncture at each visit using kits provided by Biospecimen Exchange for Neurological Disorders (BioSEND), an NIH-funded biorepository at Indiana University. If the blood draw is unsuccessful, a salivary sample is collected instead. After collection, samples are shipped to BioSEND for central storage and analysis. BioSEND will first perform genetic testing to determine the CAG repeat length within exon 1 of the *HTT* gene on chromosome 4. The number of repeats will be used to categorize study participants as either GE (≥ 36 repeats) or GNE (≤ 35 repeats). Additionally, plasma NfL concentrations will be measured using the *NF-Light® assay* with the *Simoa HD-1 analyzer* in collaboration with the Queen Square Institute of Neurology, University College of London, London, United Kingdom. Biosamples will become available to investigators via BioSEND after data collection, data analysis, and publication of primary outcome measures are complete in September of 2027.

#### Cognitive, behavioral, environmental, and motor measures.

As mentioned previously, the clinical assessment protocol is modeled after the ABCD Study [31], which tracked healthy children (9–10 years old) through adolescence. Although we are studying individuals who are both younger (6–9 years old) and older (25–30 years old), the ABCD study provides the gold standard model for large-scale studies of children and adolescents, which make up a large segment of our population of interest. Table 6 details the full assessment battery, including measures of cognition, behavioral health, environment & health, and motor function.

**Table 6 pone.0336088.t006:** ChANGE-HD assessments. MTTC = Maximum time to complete in minutes.

Domain	Test Name	Construct	MTTC	Digital	Validated Age Range/ Administered Ages
**Cognitive**	NIH Toolbox – Picture Vocabulary [45]	Language	4	Yes	• 3-85/ 6-30
	NIH Toolbox – Oral Reading Recognition [45]	Language	3	Yes	• 7-85/ 6 −30
	NIH Toolbox – Dimensional Change Task [45]	Executive function	4	Yes	• 3-85/ 6-30
	NIH Toolbox – Flanker Inhibitory Control [45]	Attention	3	Yes	• 3-85/ 6-30
	NIH Toolbox – List Sorting Working Memory [45]	Working memory	7	Yes	• 7-85/ 6-30
	NIH Toolbox – Picture Sequence Memory [45]	Episodic memory	7	Yes	• 3-85/ 6-30
	NIH Toolbox – Pattern Comparison Processing Test [45]	Processing speed	3	Yes	• 7-85/ 6-30
	NIH Toolbox – Rey Auditory Verbal Learning Task [45]	Verbal memory	3	Yes	• 8-85/ 6-30
	Controlled Oral Word Association [46]	Verbal fluency	5	No	• 6-69/ 6-30
**Motor**	Unified Huntington’s Disease Rating Scale (UHDRS) [47]	Motor	10-15	No	• 11 + / 6-30
	NIH Toolbox – 9-hole Pegboard Task [48]	Dexterity	4	Yes	• 3-85/ 6-30
	Quantitative-Motor [49]	Motor	45	Yes	• 6 + / 6-30
**Behavioral**	Achenbach System of Empirically Based Assessment [50]	Adaptive and maladaptive functioning	20	Yes	• Child Behavior Checklist Validated ages: 6–18 ◦ Administered ages: 6–17 ◦ Parent’s report • Youth Self-Report ◦ Validated ages: 11–18 ◦ Administered ages: 11–17 • Adult Behavior Checklist ◦ Validated ages: 18–59 ◦ Administered ages: 18–30 • Adult Self-Report ◦ Validated ages: 18–59 ◦ Administered ages: 18–30
	Urgency, Premeditation, Perseverance, Sensation Seeking, and Positive Urgency (UPPS-P) Behavior Scale [51,52]	Impulsivity	5	Yes	• Short version ◦ Validated ages: 14–72 ◦ Administered ages: 12–30 • Children’s version ◦ Validated ages: 7–13 ◦ Administered ages: 6–11
	Behavioral Inhibition/Behavioral Approach System (BIS/BAS) [53]	Inhibition/Reward seeking	5	Yes	• Ages 6–45/ 6–30
	Child and Youth Resiliency Measure, 5-pt scale versions [54]	Resilience	3	Yes	• Ages 6–17/ 6–17 ◦ proxy and self-report
	Adult Resiliency Measure, 5-pt scale versions [54]	Resilience	3	Yes	• 18 + / 18-30 ◦ proxy and self-report
	Sleep Disturbance Scale for Children [55]	Sleep	5-10	Yes	• 6 + / 6-30
	Sports and Activities Involvement Questionnaire [56]	Involvement in sports, music, hobbies	5-10	Yes	• 9-13/ 6-30
	Ohio State Traumatic Brain Injury Screen-Short [57]	Traumatic brain injury history	5-10	Yes	• 6 + / 6-30
	Substance Abuse and Substance Use Form (SASUF) [58]	Substance use/abuse	2	Yes	• 9 + / 12-30
**Environment and Health**	Neuro-QoL short forms [59]	Mental health	6-9	Yes	• Positive Affect and Well-being ◦ Validated Ages: 18+ ◦ Administered Ages 18–30 • Emotional and Behavioral Dyscontrol ◦ Validated Ages: 18+ ◦ Administered Ages 18–30 • Anger ◦ Validated ages: 8–17 ◦ Administered ages: 6–17
	Neuro-QoL (Quality of Life) short forms [59]	Social health	6-9	Yes	• Ability to Participate in Social Roles and Activities ◦ Validated Ages: 18+ ◦ Administered Ages 18–30 • Satisfaction with Social Roles and Activities ◦ Validated Ages: 18+ ◦ Administered Ages 18–30 • Social Relationship – Interaction with Peers ◦ Validated ages: 8–17 ◦ Administered ages: 6–17

In the Kids-HD study, cognitive evaluation relied heavily on the Wechsler scales. However, in alignment with new NIH guidelines seeking to improve the inter-rater reliability of multi-site cognitive outcomes, a protocol change was implemented to use the NIH Toolbox (Version 2) [45]. The NIH Toolbox is an iPad-based assessment tool designed to obtain comprehensive metrics from a single visit in the following domains: language, verbal fluency, executive function, attention, working memory, episodic memory, processing speed, and visuospatial intelligence. It offers several advantages, including being digital, standardized, and comprehensive, reducing variability in test results, improving the precision of cognitive measurements, and enabling comparisons across diverse ages and sites. The NIH Toolbox is also validated for use in individuals across the lifespan (ages 3–85; [45,48,59]) and is widely used to study neurological disorders and diseases, such as stroke [60] and Huntington’s disease [61,62], and other clinical populations [63]. Critically, the NIH Toolbox provides a domain-specific score based on all cognitive tests. These standardized cognitive domain scores will serve as our primary metric to assess cognitive function, although we will also explore the effects of gene expansion on each individual test.

Motor functions are assessed using the Unified Huntington’s Disease Rating Scale (UHDRS) motor battery, the NIH Toolbox Nine Hole Peg Test, and the Quantitative Motor (Q-Motor; primary outcome measure for motor performance) assessment. The Q-Motor battery assesses tapping speed and regularity of movements produced by index fingers, hands, and feet. It also quantifies grasping, lifting, and involuntary choreiform movements. The Q-Motor battery is also likely to be more sensitive to pre-manifest changes in motor performance than the UHDRS-TMS [64]. Altogether, it provides a comprehensive and precise evaluation of motor function that has been validated in children [30].

We measure behavioral metrics including participants’ adaptive and maladaptive functions, impulsivity, inhibition/reward seeking, and psychological resiliency using the Achenbach System of Empirically Based Assessment, the Urgency, Premeditation, Perseverance, Sensation Seeking, and Positive Urgency (UPPS-P) impulsive behavior scale, the Behavioral Inhibition/Approach System scale (BIS/BAS), and the Adult/Child-Youth Resilience measure, respectively. Finally, we also record participants’ physical, mental, and social well-being, sleep, the presence of sleep disorders, physical activities, history of traumatic brain injury, and substance use and abuse using Neuro-QoL (Quality of Life) [65], the Sleep Disturbance Scale for Children [55], the Sports and Activities Involvement Questionnaire [56], the Ohio State Traumatic Brain Injury Screen (short version) [57], and a substance abuse and use form (SASUF, made in-house) [58], respectively. All data collected under this protocol will be de-identified and uploaded to the NDA following data collection and analysis.

#### Magnetic resonance imaging.

Our main goal in designing the ChANGE-HD MRI protocol was to improve on the Kids-HD protocol, giving us the best chance of reproducing previous findings [17] and revealing new ones. To this end, the MRI protocol was designed to collect high resolution structural and functional MRI data within the time span of a typical research MR exam (~1 hour). To harmonize data across scanning sites, the scanning protocol was adapted from the ABCD study [31]. We used 3 Tesla research scanners to collect T1-, T2-, and diffusion-weighted, and resting-state functional MR brain images (see Table 7 for sequence parameter details). These sequences have been adapted and optimized for all six sites across Philips, General Electric, and Siemens MR scanner platforms.

**Table 7 pone.0336088.t007:** ChANGE-HD harmonized imaging scanning parameters for 3T scanners. FOV = field of view, TR = repetition time, TE = echo time, TI = inversion time, MP = MPRAGE, GR = spoiled gradient echo. VUMC = Vanderbilt University Medical Center.

Siemens (CHOP/ UC Davis)	Matrix	FOV	%FOV phase	Resolution (mm)	TR (ms)	TE (ms)	TI (ms)	Flip Angle (deg)	Parallel Imaging	Multiband Acceleration	Phase partial Fourier	b-values	Acquisition Time
**T1**	256x256x176	256x256	100	1.0x1.0x1.0	2500 (MP)	2.90	1060	8	2x	Off	Off	N/A	7:26/ 5:48
**T2**	256x256x176	256x256	100	1.0x1.0x1.0	3200	564/545	N/A	120/ Var	2x	Off	Off	N/A	4:52/ 4:42
**Diffusion**	140x140x81/ 122x122x78	240x240/ 241x241	100	1.7x1.7x1.7\ 2.0x2.0x2.0	4100/ 4170	88/ 103	N/A	88/ 90	Off	3	6/8	**CHOP**: 500 (6), 1000 (20), 2000 (20), 3000 (64). **UC Davis**: 500(6), 1000(15), 2000(60)	13:57/ 7:05
**fMRI**	90x90x60/ 86x86x60	216 x 216	100	2.4x2.4x2.4	800	30	N/A	52/67	Off	6	Off	N/A	5:00 x 4/ 4:08 x 4
Philips (**UT Houston**/ **VUMC**)	Matrix	**FOV**	**%FOV phase**	**Resolution (mm)**	**TR (ms)**	**TE (ms)**	**TI (ms)**	**Flip Angle (deg)**	**Parallel Imaging**	**Multiband Acceleration**	**Half Scan Factor**	**b-values**	**Acquisition Time**
**T1**	256x256x225	256x256/ 256x240	93.75	1.0x1.0x1.0	6 (GR)	3.0	1060	8	2 x	Off	Off	N/A	5:52
**T2**	256x256x256	256x256	100	1.0x1.0x1.0	2500	251.7/ 268	N/A	90	2.5 x	Off	Off	N/A	2:53/ 2:50
**Diffusion**	144x144x80	240x 240	100	1.7x1.7x1.7	6500	96	N/A	78	Off	3/ 4	0.603	500 (6) 1000 (15) 2000 (15) 3000 (60)	11:07/ 11:11
**fMRI**	96x96x60	230x230	100	2.25x2.25x2.4	800	30	N/A	52	Off	6	Off	N/A	5:00 x 4/ 5:15 x 4
General Electric (**Iowa**/ **Columbia**)	Matrix	**FOV**	**%FOV phase**	**Resolution (mm)**	**TR (ms)**	**TE (ms)**	**TI (ms)**	**Flip Angle (deg)**	**Parallel Imaging**	**Multiband Acceleration**	**Phase partial Fourier**	**b-values**	**Acquisition Time**
**T1**	256x256x208	256x256	100	1.0x1.0x1.0	2622 (MP)/ 2296 (MP)	2.96	1060	8	2 x	Off	Off	N/A	7:12/ 7:20
**T2**	256x256x208\ 256x256x204	256x256	100	1.0x1.0x1.0	3200/3202	60/ 55.7	N/A	Var/ 90	Off	Off	Off	N/A	6:28/ 4:58
**Diffusion**	140x140x81	240x240	100	1.7x1.7x1.7	9000/ 10000	102 \ 101.7	N/A	90	Off	2	5.5/8/ Off	**Iowa**: 500(6) 1000(15) 2000(15) 3000(60) **Columbia:** 3000 (96)	14:36/ 17:30
**fMRI**	96x96x60	307x307	100	2.4x2.4x2.4	800	30	N/A	52	Off	4/ Off	Off	N/A	5.00 x 4

As in the ABCD study, all images across sites were acquired in the axial plane because GE and Philips scanners may cause ghosting artifacts when acquired at oblique angles. Several improvements have been made to our MRI protocol since the Kids-HD study. While Kids-HD involved a single Siemens scanner at the University of Iowa, ChANGE-HD involves a mix of three vendors (Iowa: General Electric, CHOP: Siemens, Columbia: General Electric, UT Houston: Philips, UC Davis, Siemens, Vanderbilt: Philips). T1- and T2-weighted scan resolution has been increased by decreasing voxel sizes from 1.1 mm (T1) and 1.0x1.4x1.0 mm (T2) to 1.0 mm isotropic. To improve signal-to-noise ratio (SNR), we also increased the head coil channels from 12 in Kids-HD to between 32 and 48 (depending on scanner model) in ChANGE-HD.

Several improvements to resting-state functional scans were made. First, instead of acquiring one five-minute scan, we collected two scans (10 minutes total), each with opposite phase encoding directions. These improvements were made to reduce the effects of spurious noise and improve SNR [66], while reducing susceptibility effects [67]. Voxel and temporal resolution were also improved by decreasing voxel size from 3.4x3.4x4.0 mm to at least 2.4 mm isotropic and decreasing the TR from 2500 ms to 800 ms, respectively.

Finally, diffusion scanning was improved by decreasing voxel sizes from 2.0 to 1.7 mm isotropic and reducing distortion potential by lowering the echo time from 81 ms in Kids-HD to 69 ms in ChANGE-HD. Thus, the improvements in hardware and software represent a significant technological improvement between studies. Although scanning times differed by study site and participant visit, the approximate active scanning time was ~ 1 hour, including ~16 minutes for structural T1/T2 scans, ~ 18 minutes for diffusion scans, ~ 22 minutes for resting state scans, and ~2 minutes for BOLD field maps. Participants were given opportunities to take breaks and leave the bore, if needed.

During data collection periods, several quality control measures were followed to optimize scan quality. First, prior to study initiation, and once per year, each site was responsible for human phantom calibration. These calibrations were performed by designated credentialed imaging experts at each site (see S1 Table for each imaging expert). Second, each site’s imaging expert and team were required to regularly check scans for signs of poor scan quality, such as low tSNR or high resting state scan motion. In some cases, scans were repeated to ensure high image quality (e.g., the appearance of participant motion during resting state scanning). Third, deviations in protocol or changes to the study MRI system were noted by each site’s MR physicist. Post-data collection metrics of quality control will be reviewed to ensure that our final scans include only those with SNR of above 20, 45, 25, and 10 for anatomical, resting-state, b0, and b1000 diffusion scans, respectively. Resting state functional scans will be rejected if average framewise displacement exceeds 0.3 mm and frames will be censored if motion exceeds 0.3 mm.

All raw (uncensored, uncorrected, etc.) neuroimaging data collected under this protocol will be de-identified and uploaded to the NDA following data collection and analysis. Structural MRIs will be defaced to prevent participant identification.

#### Demographics and history.

Once cognitive, behavioral, motor, and environmental assessments have been administered, demographic and medical historical data are recorded. The parent or adult participant fills out demographic, family, and medical history forms in addition to completing a medication log. Finally, we record anthropometrics, including height, weight, head circumference, blood pressure, resting heart rate, and body temperature.

#### Data collection and management.

REDCap (*Research Electronic Data Capture*) is an encrypted, HIPAA-compliant web-based application used in ChANGE-HD for data entry and storage, eliminating the need for double data entry and verification. Internal audits of de-identified data are performed regularly to ensure accurate data entry and monitor interrater reliability.

### Data analysis

#### MRI processing and analysis.

Images from all sites are collected and imported into Flywheel, an infrastructure platform that allows researchers to manage, view, and analyze imaging data. Flywheel “gears” are containerized applications that automate reproducible analysis pipelines across all sites. Flywheel facilitates image sharing and automates analysis of volumetric, diffusion, and resting-state MR data. While standard quality control procedures are implemented during scanning, including image visualization, our pipelines are designed to provide quality control reports for each scan, allowing us to manually check and reject any scans identified as problematic (e.g., high motion, noise, etc.).

**Structural/volumetric analysis:** We use *volBrain’s AssemblyNetZ* [68] and *FreeSurfer* [69] on anatomical T1-weighted volumes to obtain cortical volume, surface area, and thickness, and subcortical grey region volumes. Our primary volume measures include the basal nuclei and sensorimotor cortex. Of critical consideration for structural analysis is whether a single atlas should be used between younger and older participants. For example, the contrast between white and grey matter that is critical for *FreeSurfer* segmentation differs between children 5–10 years old and adults [70], introducing segmentation biases towards grey matter in children [71,72]. Additionally, head motion is greater in children, potentially, reducing the measured grey matter volume by 4–27% in this population [73]. Moreover, the reproducibility of FreeSurfer results in children in pediatric samples is lower than adults [74]. While these limitations may affect the longitudinal trajectory of our structural analyses, we note that the critical comparison is between GE and GNE individuals. Thus, it will be critical to identify group-specific differences in segmentation, such as potential differences in motion, rather than age-specific differences, to determine how gene overexpansion affects neurodevelopment.**Structural connectivity/Diffusion MR analysis**: We use diffusion MR and diffusion tensor imaging (DTI) to measure water molecule diffusion, allowing us to infer the integrity of white matter microstructure and the developmental maturity of brain tracts. High resolution, whole brain diffusion MR is acquired with multiple diffusion sensitivities (“b-values”). To correct geometric distortions in echo planar volumes, we acquire scans with opposing phase encoding directions (AP-PA) across all sites. Diffusion MR preprocessing is performed with the QSIPrep Flywheel gear [75]. QSIPrep is an automated pipeline that performs denoising, distortion correction, motion correction, and co-registration to T1 volumes and atlas spaces. Quality assurance (QA) reports on motion, noise, and image quality are generated at the subject level for review. The output of QSIPrep is then passed to two further diffusion MR analysis gears that measure diffusion parameters such as fractional anisotropy in regions of interest (ROIs) and tractography based structural connectome metrics.**Resting-state functional connectivity MRI analysis**: During resting state scans, participants are asked to remain awake and keep their eyes open while breathing and blinking normally and blood oxygen level dependent (BOLD) signal is measured. After signal is collected, the functional organization of the brain can be inferred by regressing the BOLD time series of multiple ROIs and network against each other, where positive correlations infer synchronous communication, negative values infer asynchronous communication, and near-zero or zero values infer little or no communication. Findings from resting state data are robust and reliable, revealing consistent functional networks [76] and strong intra-subject reliability [77]. We will use data from resting-state scans to analyze and understand functional neurodevelopment in GE subjects and how it compares to GNE subjects. Resting-state fMRI preprocessing is performed with fMRIPrep [78], which provides denoising, motion correction, susceptibility distortion correction, and alignment to each subject’s T1 anatomical image and atlas space. The preprocessed data are then analyzed using eXtensible Connectivity Pipeline Developmental Cognition and Neuroimaging (XCP-D) [79], which performs nuisance regression and temporal filtering and produces brain parcellated connectivity matrices. These matrices are generated using a cortical and subcortical atlas matched to the diffusion MR atlas, enabling direct comparison between structural and functional connectivity. For the ChANGE-HD study, the primary measures are pairwise functional connectivity values and network-level metrics related to striatal-cortical circuits.

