
#### Statistical analysis using YTO Models.

We will employ a YTO model, which provides a more detailed representation of disease-related changes (between 50 and 0 YTO) than an age-based analysis [15,16,18,23]. Our statistical analyses are derived from Langbehn et al. [80] and our own work [17] investigating neural and behavioral changes across YTO. This method is based primarily on data from individuals with CAG repeats between 41 and 56 [80] but extrapolation has generalized usefully to CAG repeats extending beyond this range (40, 57–70, etc.) [17]. Because individuals with between 36–39 CAG repeats represent an incomplete penetrance group, they will be excluded from the YTO analysis and will be examined separately in exploratory analyses. Individuals with >70 CAG repeats will also be excluded as they are likely to have already begun showing motor symptoms of HD and are likely classified as patients with JOHD. All hypotheses relate to either systematic group difference between GE and GNE individuals or to differences within the GE group driven by CAG expansion length and age (or years to onset as in the NfL analysis). Our analysis approach will include the following steps: 1) age and sex correction based on the data from healthy controls, 2), estimation of YTO, and 3) YTO modeling with testing for potential additional sex differences and sex by YTO interactions.

For each dependent variable, we apply statistical corrections to separate developmental effects of typical aging from those experienced by GE individuals as part of the disease trajectory. We perform this correction by modeling age and sex effects in GNE controls using a regression that includes within-subject and within-family random effects. The models incorporate both linear and potential non-linear age relationships. Nonlinearity is modeled flexibly via restricted cubic splines (“natural splines”). The degree of non-linearity (up to five degrees of freedom) is determined by choosing the model with the lowest Akaike Information Criterion (AIC), with tied AIC values (≤ 1.0) favoring the simpler model. We also test the model for sex and sex-by-age interactions, which are excluded from the final model if found to be nonsignificant. The fitted values for this model are then subtracted from the dependent value to complete the correction.

Estimation of age of motor symptom onset is calculated using the Langbehn model [80] shown below:

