$$\begin{array}{c} Age\;of\;motor\;symptom\;onset=\text{2}\text{1}.\text{5}\text{4}-(\text{9}.\text{5}\text{5}\text{6}-\text{0}.\text{1}\text{4}\text{6}*CAG) \end{array}$$

YTO is then calculated by simply subtracting participants’ ages (in years) from age of motor symptom onset. (The abbreviation YTO, now established by precedent, stands for a slight misnomer. The value is the number of years from the mean age of onset for those with the given CAG length. It is not the individual’s number of years to onset—which is unknowable—and is slightly different from the individual’s expected years to onset, given that they have reached their current age without already experiencing onset.)

A limitation of this YTO approach is that it can only approximate the relationship between true years to HD onset and the outcome measures. As noted earlier, the YTO calculations are slightly biased estimates of participants’ expected years to onset. Furthermore, a person’s true years to onset has a probability distribution around the CAG-specific average. For concave relationships, such as those we typically expect in the neurodevelopment of brain volumes, substitution of an average value for a probability distribution causes at least slight underestimation of the predicted value that would be obtained from a model based on the true (but unknowable) number of years from onset (Jensen’s inequality).

We assess the relationship between YTO and age- and sex-adjusted outcome measures in GE individuals using an additional mixed effects regression, again including random effects for repeated measures of the same participant and for similarities between participants from the same family. Similar to the GNE model described above, the potentially nonlinear influence of YTO is modeled using restricted cubic splines with degrees-of-freedom chosen by AIC. Sex and sex interactions with YTO are tested and included in the model if significant. The mixed effect models are fitted by maximum likelihood and F-test degrees of freedom are estimated using the Satterthwaite approximation. The summary of the resulting model indicates a p-value for the effect of YTO, which, if significant, indicates a statistically meaningful difference of GE from GNE along the YTO trajectory. Finally, we plot these relationships and their 95% confidence intervals to determine where these differences occur along the trajectory (50−0 YTO)

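### The structural MRI models contain no motion or image-quality term, although the article itself calls differences in motion between GE and GNE critical to identify

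*Protocol article*

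**What the plan says.** Brain volume is the primary outcome. The article predicts larger volumes in GE than in GNE participants before 20 YTO and smaller ones from 20 to 0 YTO (Protocol article, *Power analysis and sample size calculation*).

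On motion, *MRI processing and analysis* states that "head motion is greater in children, potentially, reducing the measured grey matter volume by 4–27% in this population". It argues that the comparison that counts is GE against GNE, so that "it will be critical to identify group-specific differences in segmentation, such as potential differences in motion, rather than age-specific differences". It does not say how such a difference would be identified or what would follow from finding one.

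The safeguards for scans are in two places:

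- *Magnetic resonance imaging* describes site checks, some repeat scans and an SNR above 20 for anatomical images. Its numeric motion limits cover another modality: "Resting state functional scans will be rejected if average framewise displacement exceeds 0.3 mm and frames will be censored if motion exceeds 0.3 mm".
- *MRI processing and analysis* provides per-scan quality reports and manual rejection of problematic scans, high motion included, with no stated threshold.

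The models are in *Statistical analysis using YTO Models*. The sequence is "1) age and sex correction based on the data from healthy controls, 2), estimation of YTO, and 3) YTO modeling". The correction step consists of "modeling age and sex effects in GNE controls using a regression that includes within-subject and within-family random effects", with a spline for age and a tested sex-by-age term. The GE step has a YTO spline and the same random effects, and "Sex and sex interactions with YTO are tested and included in the model if significant". The p-value for YTO, "if significant, indicates a statistically meaningful difference of GE from GNE along the YTO trajectory". The imaging–clinical models in the same section add no motion term.

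**The concern.** The article names a bias in its primary outcome, says which form of it would matter, and then specifies models that cannot see it. The specification is detailed, down to the AIC tie rule and the Satterthwaite degrees of freedom, so the printed list of terms reads as the intended model.

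Subtracting the GNE age and sex fit removes whatever motion effect an average GNE participant of that age and sex would show. Motion that depends on gene status, or on YTO within the GE group, stays in the corrected outcome. A GE-specific motion gradient along YTO enters the YTO test directly. A constant GE-specific offset does not change the slope, but it shifts the plotted curve and its confidence band away from zero. Either would be read as a gene effect.

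The stakes are more than technical. The Discussion would take a replicated early-life advantage as support for antagonistic pleiotropy and as a reason for caution about lowering huntingtin early. A reader of that conclusion should be able to see whether motion was examined.

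**Working it through.** **1. The plan's own figures (Table 5).** The formula is NCP = (F − 2F/ddf − 1) × ndf, with F and ddf multiplied by 2.278 (= 180/79). Power comes from the non-central F at alpha 0.01.

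- Cortical gray matter: F = 12.22 × 2.278 = 27.84 (table: 27.86) and ddf = 99.90 × 2.278 = 227.57. NCP = 27.837 − 0.245 − 1 = 26.593 (table: 26.593). Power is 0.9945 (table: 0.995).
- Cortical thickness: NCP 5.612, power 0.4058 (table: 5.612 and 0.406).
- Whole brain: NCP 49.491, power 0.9999 (table: 49.491 and >0.999).
- Cerebral white matter: NCP 63.099, power above 0.999, as in the table.

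The power figures reproduce. They carry the Kids-HD F statistics forward and make no separate allowance for motion.

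**2. What GE–GNE difference would give a bias of a given size?** Suppose a share of scans is affected by motion and each affected scan loses a fraction of its volume. Then bias = (GE–GNE difference in share) × (fractional loss). The loss range of 4–27% is the article's; the shares are assumptions.

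- 5 points × 4% = 0.2%
- 10 points × 27% = 2.7%
- 20 points × 27% = 5.4%

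Conversely, a bias of 2% needs a difference of 2/27 = 7.4 points at the top of the loss range and 2/4 = 50 points at the bottom. The answer therefore depends almost wholly on quantities the article does not give.

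**3. Effect on the YTO test with no true gene effect.**

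- Article input: 180 GE participants.
- Assumed: 1–4 visits each, ages uniform from 6 to 30, CAG about 44 ± 3 (limited to 40–56), within-person correlation 0.9, between-person SD of 8, 10 or 12% of mean volume, and GE excess motion rising linearly from nil at 40 YTO to a bias of b% at 0 YTO.
- Onset age was computed as 21.54 + exp(9.556 − 0.146 × CAG). The equation as printed shows no exponential, but this form reproduces the article's own example: 48 repeats at age 8 gives 26.3 YTO and 43 repeats at age 22 gives 26.1, against a stated 26 for both.
- Model: random intercept, linear YTO, 1,000 runs per cell, two-sided 0.05 (the article's significance level).

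| Bias at onset | No motion term (SD 8 / 10 / 12%) | Motion measured exactly | Motion measured with reliability 0.7 |
|---|---|---|---|
| 0% | 0.067 / 0.051 / 0.043 | 0.038 / 0.048 / 0.059 | 0.050 / 0.035 / 0.045 |
| 1% | 0.075 / 0.063 / 0.051 | 0.046 / 0.046 / 0.061 | 0.054 / 0.054 / 0.051 |
| 2% | 0.147 / 0.115 / 0.099 | 0.043 / 0.045 / 0.042 | 0.047 / 0.055 / 0.048 |
| 4% | 0.390 / 0.288 / 0.224 | 0.052 / 0.051 / 0.042 | 0.065 / 0.069 / 0.076 |

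Simulation error near 0.05 is √(0.05 × 0.95/1000) = 0.007.

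**4. Cross-check with a step at 20 YTO.** Split the 180 participants at 20 YTO, with 20–50% nearer onset, and compare means with one value each. For SD 10% and an even split, SE = 10 × √(1/90 + 1/90) = 1.49. A step of 2% then gives a rejection rate of 0.27, and 4% gives 0.77. Over SD 8–12% and all splits, the rates are 0.07–0.13 at 1%, 0.14–0.39 at 2% and 0.43–0.92 at 4%. These exceed the rates in step 3 because a full step is a stronger contrast than a ramp. With the assumed age and CAG mix, a ramp reaching b% at onset separates the two halves by only about 0.45b. The article uses the 20-YTO split for imaging–clinical relationships and not for mean volume, so this check is only an illustration.

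**The case against.** **This is detail for the full plan, and quality control already covers motion.** The full protocol and SAP are not at hand, and a motion sensitivity analysis could sit there. Site checks, repeat scans, the SNR floor and manual rejection all limit gross motion, and staff who meet participants are blind to genotype. That stands as mitigation. It does not close the gap, because excluding poor scans is not adjustment for the motion left in those kept, and the article does print the model terms.

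**A reader might infer that motion is likely to imitate the predicted pattern at both ends of the trajectory.** The documents do not support this. The Kids-HD summary reports lower depression and anxiety and better behavioural and motor scores in GE participants far from onset. Less movement in the scanner is an inference from that, and no in-scanner motion is reported by group. Near onset, overt motor features are an exclusion, so involuntary movement in this sample is also an inference. Kids-HD found larger cerebral volume before 20 YTO with striatal and pallidal volumes comparable to GNE, and a general motion artefact does not readily explain that selectivity.

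**A reader might also take 4–27% as the size of the bias.** It is not a GE–GNE difference. It is the possible total effect in children, hedged in the text, and it concerns grey matter. Many participants below 20 YTO will be adults, and the starred primary outcomes include whole brain and white matter, which the figure covers less directly.

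**Adjusting for motion may remove a true effect.** If mHTT causes movement near onset, motion is partly a consequence of disease. This stands, and it is why the adjusted model should not be the sole criterion for the primary claim.

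**Conclusion.** The omission and the mechanism are clear from the text: neither stated model has a motion or image-quality term, and the GNE age correction cannot remove motion that differs by gene status or YTO. The possible bias falls most directly on the cortical grey-matter outcomes.

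Its size and direction are unknown. Under assumed SDs of 8–12%, the trajectory test stays near nominal at a GE-specific bias of 1% or less (0.05–0.08 at 1%). The rate becomes material from about 2% of volume (0.10–0.15) and reaches 0.22–0.39 at 4%. These rates rest on the assumed SD, bias shape, age and CAG mix, and a linear YTO model. The simulation covers excess motion near onset only, not reduced motion far from it.

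This does not show that motion explains the Kids-HD results or will explain those of ChANGE-HD. It shows that the stated analysis could not tell. The Table 5 arithmetic is not in question. The change is cheap and worth making before the analysis.

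**What to change.** 1. Prespecify one motion or quality measure per session. A T1 image-quality index from the existing pipeline is preferable. The alternative is mean framewise displacement over all resting-state runs, taken before any rejection or censoring so that the measure is not itself selected on motion.
2. Test whether this measure differs between GE and GNE and whether it changes along YTO within GE. This carries out the check the article already calls critical.
3. Report the structural YTO trajectories with and without the measure as a covariate, in both the GNE correction model and the GE model, as a sensitivity analysis.
4. If the two versions disagree, state that the result may reflect motion. Do not let the adjusted model alone decide the claim.

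The cost is a short addition to the analysis plan and some extra analysis of data already acquired. The drawbacks are an imperfect proxy, most of all if resting-state displacement stands in for motion during the T1 scan, and possible over-adjustment near onset in the adjusted version. In the simulation, a measure with reliability 0.7 still held the false-positive rate at or below about 0.08 with a 4% bias.
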